2.2. Sample size for all-cause mortality

The sample size has been calculated using mortality data and verbal autopsy results from Niakhar, and hospital based data from the Ministry of Health for Thiès district, in order to be able to demonstrate an impact on all-cause mortality.

The 10-year average mortality rate among children 3-59 months in Niakhar is about 35 per 1000 child years. However, there has been a steady decline in all-cause mortality over time so a 10-year average is a poor predictor of the mortality we expect in the 4 years of our project. In addition, the average over the last 5 years has been influenced by a major epidemic of meningitis in 1998-2000.

The mortality rate in the age group 3 months to 5 years over the last 10 years in Niakhar is as follows (Niakhar DSS database, IRD, Dakar):

Year No. Deaths Person years Rate per child per year

1993: 193 4852 0.0398

1994: 136 4859 0.0280

1995: 173 4872 0.0355

1996: 174 4939 0.0352

1997: 141 5002 0.0282

1998: 335 4971 0.0674

1999: 288 4752 0.0606

2000: 187 4802 0.0389

2001: 140 5017 0.0279

2002: 134 5149 0.0260

2003: 122 5443 0.0224

In view of the decreasing trend of mortality rates over this period, and to allow for effects of an increase in coverage of ITNs, we have assumed an all-cause mortality rate of 0.02 (20 per 1000) as the most appropriate estimate to use for sample size calculations. The percentage of deaths caused by malaria as determined by verbal autopsies in 1993-2001 was 29% in children < 5years in the Niakhar DSS area (Niakhar DSS report). This percentage has increased over time while the overall all-cause mortality rate has decreased. Verbal autopsies have limited sensitivity and specificity, but the true proportion of deaths due to malaria can be estimated if the sensitivity and specificity are known, using the formula

Ptrue = (Pobs + specificity - 1) / (specificity + sensitivity - 1)

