Korenromp et al. (Lancet Infectious Diseases 2003, 3:349) quote the sensitivity and specificity of verbal autopsies (VAs) for malaria deaths in Niakhar as 55% and 87% respectively. Adjusting for the sensitivity and specificity of the VAs technique implies a true fraction of 38% of deaths due to malaria is obtained. We have some confidence in this figure because it agrees well with the percentage of deaths in hospital that had malaria as the primary cause of death. From Ministry of Health statistics, the percentage of deaths in hospital due to malaria in the whole country among children under 5 yrs was 35% in 2000. For the Thies district, the percentages of malaria deaths under 5 years during 1997-2000 were:

1997: 37%

1998: 23%

1999: 27%

2000: 42%

The drop in the percentage of deaths due to malaria in 1998-9 is likely to be due to the meningitis epidemic, which caused a large number of additional deaths in 1998 and 1999. Thus, we have taken the true fraction of malaria deaths to be 38% based on the corrected VA data. This may be a slightly conservative estimate because it is a 10-year average and malaria-specific mortality has been increasing during this period.

If sIPTc has 90% efficacy against malaria deaths, we anticipate a 0.38 x 0.9=34% drop in all cause mortality due to sIPTc. If we assume a 70% efficacy, (reflecting incomplete coverage of 3 doses when sIPTc is delivered by routine health services rather than by trial staff) the drop would be 27%. If we have 70% efficacy and the percentage of malaria deaths turns out to be lower than we anticipate, say 30%, the drop in all cause mortality would be 21%. We have done sample size calculations for these three scenarios. Furthermore the sample size also depends on the degree of variability between zones in the all-cause mortality rate. This is usually expressed as the coefficient of variation, k. We do not have site-specific estimate of k but, for a wide range of outcomes in cluster-randomized trials, k is usually in the region of 0.25 to 0.3 (Hayes and Bennett, 1999). The table below presents sample size calculations for these scenarios, firstly assuming a coefficient of variation of 0.25, and then repeated assuming the coefficient of variation is 0.3. All calculations assume there is an average of 2000 children 3 months to 5 years in each zone.

Mortality rate True Efficacy of % reduction No. of zones for:

per 1000 % due to sIPTc against in all-cause 90% power 80% power Description

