child years malaria malaria deaths mortality

k=0.25

20 38% 70% 27% 22x2=44 16x2=32 Most likely scenario

20 30% 70% 21% 35x2=70 26x2=52 Lower % malaria deaths

25 30% 70% 27% 20x2=40 15x2=30 Higher all cause mortality

k=0.30

20 38% 70% 27% 27x2=54 20x2=40 Most likely scenario

20 30% 70% 21% 45x2=90 34x2=68 Lower % malaria deaths

25 30% 70% 27% 26x2=52 20x2=40 Higher all cause mortality

Therefore a sample size of 44 zones would give us 90% power if k=0.25 and 80% power if k=0.3, in 2 of the 3 scenarios. In the worse case scenario of low all cause mortality and lower than expected % malaria deaths, the power is more limited (44 zones would give us 61% power if k=0.3 and 72% power if k=0.25). If the all-cause mortality is higher than we predict, say 35 per 1000, which is the 10-year average figure, the worst case scenario, with 44 zones, has 78% power if k=0.25 and 65% power if k=0.3. If the all-causes mortality is 20 per 1000, but efficacy of IPT against malaria deaths is 90%, then the power for the worse case, with 44 zones, is 90%.

The study population is therefore about 95,000 children 3-59 months of age living in the 48 interventions zones.

Power calculations will be updated using themost recent data from Niakhar DSS, when these become available. An interim analysis will be done at the end of year 2; conditional power calculations will be done to in order to check the adequacy of the projected sample size.

2.3. Sample size rationale for the cross-sectional surveys in December for parasitology, parasite resistant genotypes, anemia, febrile children and malnutrition endpoints:

***Sample selection****:* 150 children aged 3 months to 5 years will be selected from each cluster (zone) for testing in December. Blood will be obtained for hemoglobin, thick smear for microscopy, and parasite genotyping, and assessment of nutritional status will be made. In each zone, children will be selected using a 2-stage cluster sampling design. Communities will be selected with probability proportional to size, and a fixed number of children selected from each selected community from the village register by systematic sampling.

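### The 90% power given for the worse case with 90% efficacy holds at k = 0.25 only; at k = 0.30, 44 zones give about 83%

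*Combined protocol and SAP*

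**What the plan says.** Everything is in protocol section 2.2 (sample size for all-cause mortality).

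- **The statement at issue.** "If the all-causes mortality is 20 per 1000, but efficacy of IPT against malaria deaths is 90" per cent, "then the power for the worse case, with 44 zones, is 90" per cent. No value of k is given.
- **The worse case.** It is introduced two sentences before: "In the worse case scenario of low all cause mortality and lower than expected % malaria deaths". The lower malaria fraction is set earlier in the section, where the "percentage of malaria deaths turns out to be lower than we anticipate, say 30" per cent. Neither place makes k part of the definition.
- **The range of k.** There is no site-specific estimate. The section relies on general experience that "k is usually in the region of 0.25 to 0.3", and the table has one block for each of those two values.
- **The table row for a 27% reduction at 20 per 1000, k = 0.30.** "20 38% 70% 27% 27x2=54 20x2=40 Most likely scenario". The two zone counts are for 90% and 80% power. The matching row at k = 0.25 gives 44 and 32 zones.
- **The other powers in the paragraph, all for 44 zones.** They are 90% and 80% for two of the three scenarios, 72% and 61% for the worse case at 70% efficacy, and 78% and 65% for the worse case at 35 per 1000. The first of each pair is for k = 0.25 and the second for k = 0.30.

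**The concern.** The sentence offers reassurance: even if malaria causes fewer deaths than expected, a highly effective drug brings power back to 90%. It is the only power in the paragraph without a k, and a reader would naturally take it to hold over the whole range considered. The table says otherwise for the same effect size. All-cause mortality is the primary endpoint and k was unknown at planning, so k = 0.30 was as plausible as k = 0.25. If k is 0.30, the probability of missing a true 27% reduction is well above the 10% implied.

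**Working it through.** **Inputs**

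| Quantity | Value | Source |
|---|---|---|
| Control rate, λ0 | 0.02 per child-year | section 2.2 |
| Malaria share of deaths, worse case | 30% | section 2.2 |
| Efficacy against malaria deaths | 90% | the sentence at issue |
| k | 0.25 and 0.30 | section 2.2 |
| Zones per arm, c | 22 (44 in all); 24 for 48 | section 2.2 |
| Child-years per zone, y | 2000 | 2000 children per zone (section 2.2); one year of comparison each is assumed |
| Significance level | two-sided 5% | assumed; not stated for mortality |

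**Step 1: check against the table, with no formula.** The reduction is 0.30 × 0.90 = 27%. The most likely scenario is 0.38 × 0.70 = 26.6%, which the plan rounds to 27%, at the same 20 per 1000. At k = 0.30 that row needs 54 zones for 90% power and 40 for 80%. Since 40 < 44 < 54, power with 44 zones must lie between 80% and 90%.

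**Step 2: formula.** The standard expression for comparing rates in an unmatched cluster-randomised trial is

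c = 1 + (z for α/2 + z for power)² × V, where V = [(λ0 + λ1)/y + k²(λ0² + λ1²)] / (λ0 − λ1)².

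Solved for power: Φ(√((c − 1)/V) − 1.96).

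**Step 3: reproduce the plan's other figures.**

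| Plan's figure | Stated | Recalculated |
|---|---|---|
| Zones per arm, 27% reduction, 90% power, k = 0.25 | 22 | 21.0 |
| Same, k = 0.30 | 27 | 27.1 |
| Worse case (21%), 44 zones, k = 0.25 / 0.30 | 72% / 61% | 71.1% / 59.6% |
| Worse case at 35 per 1000, k = 0.25 / 0.30 | 78% / 65% | 77.0% / 64.1% |

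The stated powers are matched within 2 points, which supports the assumed significance level and person-time.

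**Step 4: the sentence at issue.** λ1 = 0.02 × 0.73 = 0.0146.

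- (λ0 + λ1)/y = 0.0346/2000 = 0.0000173
- λ0² + λ1² = 0.0004 + 0.00021316 = 0.00061316
- (λ0 − λ1)² = 0.0054² = 0.00002916
- k = 0.25: V = (0.0000173 + 0.0625 × 0.00061316)/0.00002916 = 1.907
- k = 0.30: V = (0.0000173 + 0.09 × 0.00061316)/0.00002916 = 2.486

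| Zones | k = 0.25 | k = 0.30 |
|---|---|---|
| 44 (c = 22) | Φ(√(21/1.907) − 1.96) = 91.3% | Φ(√(21/2.486) − 1.96) = 82.8% |
| 48 (c = 24) | 93.5% | 86.0% |

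The stated 90% is therefore the k = 0.25 result. With 44 zones, 90% power is kept only up to about k = 0.26.

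**Step 5: can another reading give 90% at k = 0.30?**

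| Variant, 44 zones, k = 0.30 | Power |
|---|---|
| Omitting the +1 | 84.5% |
| t reference distribution, with / without the +1 | 81.0% / 82.8% |
| Doubling person-time to y = 4000 | 87.2% |
| One-sided 5% | 89.6% |
| 38% malaria deaths, so a 34% reduction | 96.7% |

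One-sided testing comes close, but it gives 95.3% at k = 0.25 and does not fit the plan's zone counts or other powers. The last variant is not the worse case, and it is not 90% either.

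**The case against.** The strongest reply is that nothing was miscalculated. Ninety per cent is right at k = 0.25, the sentence never claims it for k = 0.30, and what is missing is a qualifier. The k = 0.30 result can also be recovered from the same section: the table row shows it, and the paragraph opens by giving 80% at k = 0.30 for a scenario with practically the same effect. No decision depends on the sentence, because the sample size comes from the 70% efficacy rows and 48 zones are planned. The protocol treats k as provisional: a pilot survey is to estimate it, and power is to be updated. Stratification by expected mortality may also add precision that the unmatched formula ignores, although the documents do not quantify this.

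Most of that is fair, and it sets the weight of the point. It does not rescue the sentence: a power that changes by about eight points over the plan's own range of k cannot be given as one number when its neighbours are given as pairs.

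A second objection is about precision. The plan's other worse-case powers lie between the results with the +1 and without it (92.5% and 84.5% in this case), so replacement figures carry about one to two points of method uncertainty. That stands, and it is why the fix says *about*.

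**Conclusion.** The concern holds, as a minor point. With 44 zones, the worse case at 90% efficacy has about 91% power if k = 0.25 and about 83% if k = 0.30, so the stated 90% is right at one of the plan's two values and roughly seven points too high at the other. The type II error at k = 0.30 is about 17% instead of 10%. That 90% is not reached at k = 0.30 follows from the plan's table alone. The exact percentages rest on the unmatched formula, two-sided 5% testing and one child-year per child, none of which the protocol states for mortality but which together reproduce its neighbouring powers within 2 points. Power remains above 80% in every case considered, so neither the number of zones nor the design is put in doubt.

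**What to change.** Replace the unconditional figure in section 2.2 with one for each k, for example:

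> With 20 deaths per 1000 child-years, 30% of deaths due to malaria and 90% efficacy, 44 zones give about 91% power if k = 0.25 and about 83% if k = 0.30 (93.5% and 86% with all 48 zones).

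The section should also state the significance level, its sidedness and the person-time per zone, so that readers can reproduce the figures. If the original power program is still available, rerun it for this case so that the new pair matches its neighbours to the point. The cost is one sentence and a slightly less favourable figure at k = 0.30; sample size, conduct and analysis are unaffected.

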2.4. Malaria morbidity

Malaria cases will be treated at health centres, where treatment is with AQ/AS based on presumptive clinical diagnosis.,

3. Drug administration

Delivery of sIPTc will be the responsibility of the National Malaria Control Programme. It is planned that in each village two to six persons will be trained to give preventive treatment to children on 1st September, 1st October and 1st November, or on the nearest appropriate day, and to record in the register the children who received preventive treatment. The community will designate these persons and the nurse will be responsible for their training in correct drug administration. The nurse will provide drugs in advance to the chief of the village. Deaths occurring during the trial will be recorded immediately in the register with a record of the date of death. The operational details will be piloted in 2005. Children will be issued with a malaria card similar to the vaccination card bearing their name and ID and on which treatments will be recorded.

The choice of drug combination to be used in the main trial is SP/AQ, based on the results of a study undertaken in Niakhar in 2004 in which 2102 children were randomized to receive sIPTc with one of four drug combinations (1) SP x 1+ artesunate x 1; (2) SP x 1 + artesunate x 3; (3) SP x 1 + amodiaquine x 3 and (4) amodiaquine x 3 + artesunate x 3. SP/AQ was significantly more effective in terms of malaria incidence and parasite prevalence ([name] et al., in preparation), and its use allows artemisinins to be reserved for treatment of clinical malaria cases where their rapid action will be of most benefit. A report of this trial has been submitted to the BMGF, and a paper has been prepared for publication.

4. Community participation

The minimum community participation required from villages benefiting from the trial will be the identification of persons to keep the register and to give preventive treatment to children.

In order to stimulate additional community participation for the maximum effectiveness of the trial, a special budget will be allocated to each intervention zone under the responsibility of study nurse. He or she will decide, in agreement with the community leaders, how this budget could be best used for public health education and advocacy. This will be noted on a specific form.

5. Treatment of episodes of illness

Parents or guardians of children enrolled in the study will be encouraged to bring their children to the health post for any episode of illness that occurs during the trial. Antimalarial treatment with AQ/AS will be provided by government staff in health posts according to the national guidelines. Children who present with an acute febrile illness with no other obvious cause of the illness will be treated presumptively for malaria. All consultations of children, their symptoms on presentation and treatments received will be noted in a register.

6. Phased introduction of the intervention

***- Administration of sIPTc***

In the first year of the trial, registers of eligible children will be established in Stratum A comprising 16 zones. sIPTc will be administered in only 8 of these zones, selected at random. Throughout the study area antimalarial treatment according to the national guidelines will be available in the health post (Figure 3).

In the second year of the trial, the intervention will be extended to the remaining 8 zones of Stratum A and also it will be introduced in 8 new zones in Stratum B.

In the third year of the trial, intervention will be extended to the remaining 8 zones of Stratum B and to 8 new zones in Stratum C.

In each stratum, implementation will be taken over by the Ministry of Health and the trial communities in the second year of implementation.

**Figure 3**: A simplified model of the study design and diverse types of comparison.

***- Age at inclusion***

The minimum age for inclusion in the trial will be three months. All other children under five years of age will be eligible for the trial. In the second and the third year of the trial, children previously enrolled in the trial but who have reached their fifth birthday will be excluded from sIPTc.

7. Scaling-up ITN coverage in the study area

It will be important to ensure that ITN coverage in the study area is high in order to be able to demonstrate that IPTc provides significant additional protection in children using ITNs. It is likely that the effects of the two interventions will be additive. In a split-plot design trial in Sierra Leone, villages were randomised to receive ITNs or no nets, and within each village children were randomized to receive prophylaxis with dapsone / pyrimethamine or placebo once every 2 weeks. The effects of the exclusive use of either ITNs or prophylaxis on protection against clinical malaria due to P. falciparum was similar (49% and 42%, respectively), while in combination this protective efficacy was significantly increased to 72% (Marbiah et al. 1998). Assuming additive effects, we expect IPTc, which has efficacy of 90-95% in recent efficacy trials in Niakhar, will reduce malaria incidence and malaria mortality by this percentage in children using ITNs.

ITN coverage in the study area has increased in recent years. Surveys conducted by NetMark in 2000 and 2004 in Dakar, Thies, Saint Louis, Kaolack and Tambacounda showed that the number of households that owned a net increased from 34% (2000) to 56% (2004). In 2004, 24% of children under 5 years of age slept under an ITN the night before the survey. In Mbour district, there is no recent assessment of the use of nets, but with the intervention of CCF/Canah, the coverage rate is expected to be high. The peripheral market is dominated by highly subsidized ITNs sold in the health structures (health centres or health posts). In 2005, very few nets were distributed free. Four types of ITN share the Senegalese market (3 conventional and one long lasting Permanet) distributed through pharmaceutical companies and the private sector. To maximise ITN coverage the National Malaria Control Programme in collaboration with UNICEF will provide treated nets at substantially subsidized cost from 2006, and the project will facilitate the distribution of ITNs at the community level by working in close collaboration with local partners. In the last coordination’s meeting held at the University of Dakar in June 2005, it had been suggested that the Minister of Health form a steering committee, which will oversee all IPTc implementation studies in the country. This steering committee would also help to prioritise the study area for scaling up ITN coverage in collaboration with UNICEF, WHO, JICA, USAID and NGOs activities and through the National Malaria Control Programme. Several technical meetings are being held with the senior staffs of the Ministry of health, or the coordinator of the National Malaria Control Programme and with the local representative of UNICEF in Dakar.

ASSESSMENT OF THE IMPACT OF THE INTERVENTION

1. Process measurements

The following measurements will be made each year:

**- Proportion of eligible villages where a register of eligible children is held.**

Criterion used: presence of a register in the village (all 725 villages investigated).

**- Proportion of eligible villages, which participated fully in the study**.

Criterion used: number of villages in which at least 50% of the total number of resident children according to the results of the 2002 national census have been included in the registers (all villages investigated). Reasons for non-participation will be investigated through community focus group discussions.

**- Proportion of eligible village where drugs for sIPTc were available on the 1st September, 1st October and 1st November each year.**

Criterion used: presence of drugs for sIPTc at these three dates in villages with sIPTc (all 725 villages investigated according to year).

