### SENEGAL

Guinea Bissau

Guinea Republic

TRIAL DESIGN

1. Study population

The study population will number approximately 450,000, including 95,000 children under the age of five years (2002 national census). The study area will be divided into 48 intervention zones, each one corresponding to one health post and its related villages. On average, 15 villages and 1975 children under five years of age will be the responsibility of each health post. The chief of the village, or a person designated by him, will establish a register of eligible children. This will be done under the supervision of the nurse in charge of the health post. This register will remain permanently in the village and a copy will be kept in the health post. Community consent will be obtained for the sIPTc intervention; individual consent will be sought from parents or guardians from a subgroup for participation of children in cross-sectional surveys.

Recent surveys conducted by NetMark show that coverage of Insecticide Treated Nets (ITNs) has increased in the study area and this is expected to increase with the widespread provision of ITNs at highly subsidized cost.

2. Design, sample size and power calculations

Due to logistic constraints and the need for staff training and community sensitization, it is not feasible to introduce the intervention in all zones simultaneously and it must be phased in gradually. This provides the opportunity for evaluation by comparing intervention areas with areas that have not yet received the intervention. The order of implementation will be randomized to permit unbiased comparison of mortality rates. To enable the most efficient evaluation, zones will be grouped into strata of zones such that mortality rates are as similar as possible in the zones within each stratum, using the best proxies available for the under 5 mortality rate. We plan phased introduction over 3 years, so there are three strata, the order of implementation of sIPTc in each stratum will be determined by randomization (Figure 2). The definition of the strata, and the order in which strata receive the intervention, will be decided in close consultation with the Ministry of Health. The project statistician will determine the order of implementation within strata.

Figure 2: Phased introduction of the implementation in the population divided onto 3 strata

Stratum A B C

Year 1 X0

Year 2 XX X0

Year 3 XX XX X0

Year 4 XX XX XX

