**Baseline survey and implementation study preparatory phase**

1st July 2006 – 31 March 2007

Intervention

1st April 2007 – 31 August 2007 preparatory phase 2

1st September 2007 – 31 November 2007 intervention year 1

1st December 2007 – 31 August 2008 preparatory phase 2

1st September 2008 – 31 November 2008 intervention year 2

1st December 2008 – 31 August 2009 preparatory phase 3

1st September 2009 – 31 November 2009 intervention year 3

Evaluation

1st April 2007 – 31 August 2007 preparatory phase

1st September 2007 – 31 August 2008 evaluation year 1

1st September 2008 – 31 August 2009 evaluation year 2

1st September 2009 – 30 June 2010 final evaluation

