The mortality rate ratio for the effect of IPTc will be estimated using Poisson regression with a gamma-distributed random effect for the cluster. An indicator variable for the intervention effect in each age group (3-59 months and 60-119 months) will be defined, set to 1 for each time period, age group and cluster when IPTc was implemented and set to 0 otherwise. A test of interaction will be done and combined estimate of intervention effect estimated if there is no evidence of an interaction. Age group (<3 months, 3-59 months, 60-119 months), and calendar year (2008,2009,2010) and zone will be included as covariates in the model. All deaths recorded in the DSS system will be included with person time obtained from the DSS. The DSS here refers to the DSS system set up for this project, and the Niakhar DSS. Person time includes all persons resident in the DSS area, from study start, date of birth or immigration, and censored when they left permanently or died. Temporary absence will not be accounted for as these dates are judged to be not sufficiently accurate and complete in the project DSS. Data updated to DSS round 4 will be included in the primary analysis.

Time periods:

Primary analysis of rates will be for the period from September 15 to December 15 each year. Secondary analysis will be done using data for the whole year.

Malaria incidence:

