50 SALY, 51 SANTESSOU, 54 VAREDO) for this reason population denominators for the rebound analysis were obtained by projection from the 2008-2010 data assuming a uniform annual growth rate of 3.6%.

Incidence the year after intervention will be compared between PSP and control areas in age groups that reflect the number of previous years of IPTc received, using a random effects poisson regression with adjustment for age effects.

Estimates of the coefficient of variation between clusters will be estimated for the main incidence rate endpoints (mortality and malaria), as √α where α is the variance of the exponentiated random effect reported by Stata in the xtpoisson output, from a model without covariates and from a model with covariates.

Analysis of cross-sectional surveys:

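### Full village participation is judged each year against an un-updated 2002 census child count that is not matched to the eligible ages, so the 50% bar loosens over time wherever the child population has grown

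*Combined protocol and SAP*

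**What the plan says.** In the protocol, under Assessment of the Impact of the Intervention, 1. Process measurements, the list opens with "The following measurements will be made each year". The second item is the proportion of eligible villages that participated fully. A village meets the criterion if, on its register, "at least 50% of the total number of resident children according to the results of the 2002 national census have been included".

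The protocol's Time Table runs from "1st September 2007 – 31 November 2007 intervention year 1" to "1st September 2009 – 31 November 2009 intervention year 3". The SAP analyses 2008, 2009 and 2010. Neither document provides for ageing, projecting or replacing the census count.

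The ages are not aligned either:

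- The criterion gives no age limits for resident children.
- The section on the study population attributes 95,000 children under five to the 2002 census. The Summary gives the same 95,000 as children aged 3 to 59 months.
- The register starts at three months (Age at inclusion).
- The SAP adds a 60-119 month group to the mortality outcome and treats children up to about ten years as eligible in 2009 and 2010.

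The only growth rate in either document is in the SAP, under Malaria incidence. Denominators for the rebound analysis are "obtained by projection from the 2008-2010 data assuming a uniform annual growth rate of 3.6" per cent.

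**The concern.** The numerator is a current register and the denominator is frozen. If the number of children rises, a village that registers a constant share of its current children moves closer to the bar, or over it, each year without doing anything better. The measure can then overstate participation from the first year and show an improvement that is only demographic. The fastest-growing villages pass most easily, and a shrinking village faces a stricter test.

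Whether seasonal treatment can be delivered effectively is the first specific objective, and this is one of its yearly measures. It is also the only village-level criterion that tests how complete the register is. The neighbouring delivery criterion takes the register itself as its denominator, so it cannot detect children who were never listed.

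**Working it through.** The 50% bar is a definition, so the plan has no computed figure to reproduce. The check asks what the bar becomes as a share of current children.

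**Formula.** With annual growth g in resident children, the effective bar in year y is 50% / (1+g)^(y-2002).

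**Growth rates the documents can supply.**

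- *Niakhar person-years, ages 3-59 months* (protocol, 2.2 Sample size for all-cause mortality): 4852 in 1993 and 5443 in 2003. (5443/4852)^(1/10) - 1 = 1.16% a year. Niakhar adjoins the study area but is not part of it. Its growth is uneven: from 4802 in 2000 to 5443 in 2003 is (5443/4802)^(1/3) - 1 = 4.3% a year.
- *The SAP's 3.6%*, stated for the rebound denominators only. It is borrowed here as an assumption.

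**Effective bar, growth only.**

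| Growth a year | 2007 | 2008 | 2009 | 2010 |
|---|---|---|---|---|
| 0% | 50.0% | 50.0% | 50.0% | 50.0% |
| 1.16% | 47.2% | 46.7% | 46.1% | 45.6% |
| 2% | 45.3% | 44.4% | 43.5% | 42.7% |
| 3.6% | 41.9% | 40.4% | 39.0% | 37.7% |

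For 2009, for example, 1.0116^7 = 1.084 and 50/1.084 = 46.1%; 1.036^7 = 1.281 and 50/1.281 = 39.0%. The 2010 column reflects growth alone and takes no account of the wider eligible ages in the SAP.

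**Infants under 3 months.** If the census count covers 0-59 months, it includes infants who cannot be registered, which raises the bar as a share of eligible children. Assume 57/60 of under-fives are eligible, so divide by 0.95:

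| Growth a year | 2007 | 2008 | 2009 |
|---|---|---|---|
| 1.16% | 49.7% | 49.1% | 48.6% |
| 3.6% | 44.1% | 42.6% | 41.1% |

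At the Niakhar rate the two mismatches nearly cancel. At 3.6% they do not.

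**Older children.** If the 2009 registers also listed children aged 5-9 years while the census count stayed at under-fives, the bar would fall much further. Assuming 5-9s number 70% to 100% of under-fives, at 3.6% growth it is 39.0/1.7 = 23% to 39.0/2 = 20%. The documents do not say that this criterion was applied to the wider age group, so this only shows how sensitive it is to an undefined age range.

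**Effect on the reported proportion.** This depends on how many villages lie between the lowered bar and 50%, which the documents do not give. Two illustrations assume normally distributed village coverage:

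- *Mean 70%, SD 20%.* A true 50% bar passes 84% of villages. In 2007, 2008 and 2009 the 2002 denominator passes 87%, 88% and 88% at 1.16% growth, and 92%, 93% and 94% at 3.6%.
- *Mean 90%, SD 10%.* Virtually every village passes under either bar, and nothing changes.

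**The case against.** A reader might infer that the bar simply is 42%, 40% and 39%, and that the reported proportion must be too high and must rise. The documents do not support that.

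- The 3.6% was stated for projecting from 2008-2010 data, not for children in each village since 2002. The one local series of child numbers gives about 1.2% over ten years, and hence a fall of about 4 points by 2009 instead of 11.
- The infant mismatch works in the opposite direction. If resident children meant a wider age range than the register, the direction could reverse.
- Inflation needs growing villages with coverage between the lowered bar and 50%. None are shown to exist.
- Registers are set up stratum by stratum, starting with 16 of the 48 zones. A yearly proportion over all 725 villages would rise with the roll-out anyway.
- Delivery is also measured by doses received and by drug in the blood of sampled children. The SAP does not list village participation as an outcome, and it estimates coverage from weighted surveys that do not use the census.

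All of this stands, and it limits the size and importance of the point. It does not remove the defect. The rule as written divides a current count by one that is never updated and has no defined age range, and the other delivery measures do not correct it. The roll-out effect is a separate distortion and does not offset this one.

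**Conclusion.** The denominator is stale and not matched to the eligible ages. With any growth in child numbers, and a census count covering the same ages as the register, the bar is below 50% and keeps falling. The documents support a range: about 47%, 47% and 46% in 2007-2009 at the Niakhar rate, and 42%, 40% and 39% if 3.6% applied from 2002. Each set is about 2 points higher if the census count includes infants under 3 months, which brings the Niakhar figures close to 50%.

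The reported proportion tends to be too high and to drift upward where villages are growing and lie near the bar. How far cannot be derived from the documents. This is a secondary process indicator and the mortality analysis does not depend on it. The reason to correct it is that a yearly measure of the first specific objective can show improvement without any change in performance, and that correcting it costs little.

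**What to change.** In the participation criterion under Process measurements, keep the 50% bar but replace the 2002 census count. The denominator should be the number of resident children in that village who are eligible in the same season, taken from the project DSS. State the age range, and use the same range for the register count.

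The protocol sets up no surveillance system for the study villages. The project DSS appears only in the SAP, whose analyses cover 2008-2010. Where no DSS count exists, such as a 2007 season, use the 2002 count restricted to the eligible ages and projected forward. State the growth rate as an assumption and show the result over a range, for example from about 1.2% to 3.6%.

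The cost is a short change of wording and, for seasons without a DSS count, a small sensitivity table. The SAP already plans DSS estimates of child population size. The reported proportion may be slightly less favourable.
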